#### Dropout criteria

1. The occurrence of serious adverse events, complications and special physiological changes, it is not suitable to continue to receive the trial2. The trial process of self-withdrawal3. Due to a variety of reasons caused by the end of the course of treatment, namely, withdrawal from the trial, lost to visit the case4. Incomplete information, affecting the effectiveness and safety of the judgment.The reason for removal should be recorded in all cases of exclusion or detachment. Any adverse reactions during treatment are included in the adverse reaction statistics.

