#### Removal criteria

1. Cases in which subjects were found after enrollment not to meet the inclusion criteria2. Use of other medications related to the disease under study3. Those who, after enrollment, were not treated in accordance with the provisions of this study4. Cases in which there was no evaluable record of any post-treatment period.

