### Outcome assessment

Independent assessors, who received standardized training prior to study involvement and remained blinded to group allocations throughout the trial, will evaluate all clinical outcomes. Comprehensive participant data - including both completers and those who discontinued intervention - will be systematically documented in electronic case report forms (CRF), ensuring complete tracking of all enrolled subjects.

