### Primary outcome

Drawing on a range of clinical studies, the assessment will be carried out on all patients. Specifically, for patients with APE (Premature Ejaculation), the mean changes from the baseline (the day when the patient commences the protocol) to the end of the observation period (the day when the protocol concludes) will be evaluated in two aspects: the brain MRI and the intravaginal ejaculatory latency time (IELT) measured using a stopwatch, which has been extensively applied and is recommended as a primary outcome measure in clinical trials for APE.

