### Data analysis

#### Clinical variables analysis

Two blinded evaluators will conduct the analysis of clinical data using SPSS 22.0 (SPSS Inc., Chicago, IL). Missing data analysis will be carried out in accordance with the intention - to - treat (ITT) principle, taking into account the baseline characteristics.

The clinical scores of the subjects will be examined through Pearson correlation analysis. All clinical data in this study will be presented in the following ways:1. Continuous measurement data will be presented as the mean ± standard deviation (SD), along with the mean, SD, median, and interquartile range.2. Categorical data will be presented as counts and percentages.

The following analysis tools will be employed: the Cochran - Mantel - Haenszel (CMH) test or nonparametric test, an independent samples t - test, and a two - sided test. Additionally, analysis of covariance, covariance analysis, generalized estimating equations, chi - square (
$x^{2}$
) tests, and linear regression will be applied to all available and appropriate data. A P - value <0.05 will be considered statistically significant.

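### The dropout criteria do not separate stopping the capsules from leaving the trial, so early stoppers risk having no week-4 outcome, against the stated tracking and intention-to-treat principle

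*Protocol article*

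**What the plan says.** All places are in the protocol article.

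- **Dropout criteria.** Criterion 1 covers serious adverse events, complications and special physiological changes after which "it is not suitable to continue to receive the trial". Criterion 3 reads "Due to a variety of reasons caused by the end of the course of treatment, namely, withdrawal from the trial, lost to visit the case". On what is then recorded, the section says "The reason for removal should be recorded in all cases of exclusion or detachment", and adds that adverse reactions during treatment are counted. It names no outcome assessment.
- **Removal criteria.** These also take out "Those who, after enrollment, were not treated in accordance with the provisions of this study" and "Cases in which there was no evaluable record of any post-treatment period".
- **Table 1.** IELT, MRI, PEP, CIPE and the item ZYZHPF (which I take to be the TCM syndrome score) are marked at enrolment and week 4 only. Adverse events are marked in weeks 1 to 4, with a call-back in week 5.
- **Primary outcome.** Change runs from baseline to "the end of the observation period (the day when the protocol concludes"). No other end point is given for a patient who stops early.
- **Outcome assessment.** What is collected on patients is described as "including both completers and those who discontinued intervention - will be systematically documented in electronic case report forms (CRF), ensuring complete tracking of all enrolled subjects".
- **Clinical variables analysis.** "Missing data analysis will be carried out in accordance with the intention - to - treat (ITT) principle", with baseline characteristics taken into account.

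**The concern.** A patient can stop study medication and still be followed, or he can leave the study. The Dropout criteria have one category for both. With a single post-baseline outcome point, a patient closed out before week 4 contributes no change in IELT and no second scan. An analysis plan can choose how to handle missing values, but it cannot recover a measurement that nobody took.

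This matters most if stopping differs between arms. The Abstract and Introduction say that SSRIs carry side effects and poor compliance, and two of the four arms (42 of 84 patients) receive paroxetine. If more men stop there, a comparison of those still on treatment at week 4 sets men who tolerate paroxetine against a less selected placebo group. It would then overstate the effect in all randomised patients.

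**Working it through.** **1. The sections side by side**

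| Question | Dropout criteria and Table 1 | Outcome assessment and Clinical variables analysis |
|---|---|---|
| Is stopping capsules distinct from leaving the trial? | No separate category | Discontinuing intervention is named as a status within the tracked population |
| What is recorded after a stop? | Reason and adverse reactions | Participant data, with all enrolled subjects tracked |
| When are outcomes measured after baseline? | Week 4 only, no visit on stopping | Not stated |
| Who is analysed? | Not stated | Intention-to-treat principle |

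Take a man who stops in week 2 and is classed as a dropout. The left column gives a site no instruction to see him at week 4. The right column cannot be honoured for the endpoints unless someone does. No section says that he will be invited, and none says that he will not.

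**2. The plan's own numbers**

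Four groups of 21 give 4 × 21 = 84, as stated. The Study design section says 15 per group are needed, so the allowance is 21 − 15 = 6 per group, or 6/21 = 28.6%. It covers both dropout and scans spoiled by head movement. No dropout rate by arm is given.

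**3. Illustration of size**

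These assumptions are not in the document: a 3-fold IELT gain in patients who stay on drug, no gain in those who stop, no change and no stopping on placebo, and an analysis of completers only. With s stoppers among 21:

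- Effect in completers: 3.0-fold, log effect ln 3.
- Effect in all randomised: exp[ln 3 × (1 − s/21)].
- Overstatement on the log scale: 1/(1 − s/21).

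| s | All randomised | Completers | Log-scale overstatement |
|---|---|---|---|
| 2 | 3^(19/21) = 2.70-fold | 3.0-fold | 21/19 = 1.11 (11%) |
| 3 | 3^(18/21) = 2.56-fold | 3.0-fold | 21/18 = 1.17 (17%) |
| 6 | 3^(15/21) = 2.19-fold | 3.0-fold | 21/15 = 1.40 (40%) |

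The overstatement depends on the fraction stopping and on stoppers gaining nothing. It does not depend on the 3-fold figure. Any benefit that stoppers keep makes it smaller. The last row spends the whole allowance on early stopping and leaves nothing for head movement, so it is an upper end within the plan's own allowance.

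**The case against.** A reader might infer that early stoppers will have no post-baseline IELT or MRI. The document does not say so. Table 1 marks week 4 without exempting anyone, and Outcome assessment points towards following those who discontinue. This stands: the loss would come from how a site applies the dropout wording.

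Criterion 3 is poorly phrased. It can be read as listing courses that ended because the patient withdrew or was lost, which is what dropout criteria normally contain. Criterion 1 concerns serious events, so an ordinary side effect need not meet it, and its wording could mean only that treatment ends. These readings are fair. They weaken the point but do not remove it, because on any of them the protocol still does not say whether a man who stops capsules is seen at week 4.

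It is also tempting to say that no missing-data method could repair the loss. That goes too far. If stoppers gain nothing, carrying their baseline value forward gives exactly the all-randomised results above (2.70, 2.56 and 2.19). The method may be in an analysis plan that is not shown, and weekly adverse-event records give some on-study information. What remains is that the no-gain assumption cannot be checked without the week-4 values.

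The illustrative assumptions all push in one direction. Every arm carries the same capsule load, so stopping because of burden could be similar across arms. Bias in favour of paroxetine over CHSGS would need fewer stops on CHSGS, and no stopping rate is given for either.

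Finally, an article may leave an early-termination visit to the full protocol. That absence is not held against it here. The point rests on the printed dropout wording, which sits badly with two other printed statements.

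**Conclusion.** The point holds as an inconsistency that should be fixed. The Dropout criteria merge stopping treatment with leaving the trial: plainly enough for serious adverse events, and on one reading for any ended course. Applied as written with a single week-4 outcome point, they could leave early stoppers without data that the tracking and intention-to-treat statements presuppose. The Removal criteria point the same way, but removing patients already enrolled is a separate matter from failing to collect their outcomes.

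The document does not support the stronger conclusion that these outcomes will be absent. The size of any bias is unknown. The 11% to 40% range illustrates a completers-only analysis under assumed values and is not an estimate for this trial. It requires stopping to differ by arm, which the protocol's remarks on SSRI tolerability make plausible but do not quantify.

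**What to change.** Reconcile the Dropout criteria with Outcome assessment and Clinical variables analysis:

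1. Define two statuses: stopped study capsules (any reason, including an adverse event), and withdrew consent or was lost to follow-up.
2. State that patients in the first status remain in the trial for data collection and are still asked to attend the scheduled week-4 IELT, PEP, CIPE and TCM syndrome score, and the MRI if willing and fit.
3. State that only the second status ends outcome collection.
4. Analyse the values in the arm as randomised.

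This concerns data collection only and leaves the decision to stop treatment as it is. No extra assessment on the stopping day is proposed, since a stopwatch IELT depends on intercourse and cannot be taken on demand.

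The cost is a few sentences and one case report form field, as the week-4 assessments are already planned for every patient. The downside is that some week-4 values will be measured off drug. The estimate then describes the effect in all randomised patients and will be somewhat smaller than the effect in those who stay on treatment.

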### Randomized

Eligible participants will be randomly allocated to one of four groups in a 1:1:1:1 ratio: the paroxetine group, CHSGS group, CHSGS + paroxetine group, or placebo group. Randomization will be performed using SAS V.9.3 software, with sequences generated by an independent third party not involved in participant management, outcome assessment, or data analysis. Group assignments (denoted as A, B, C, or D) will be sealed in sequentially numbered, opaque envelopes prepared by a researcher unaffiliated with the trial. These envelopes will remain securely stored in numerical order until the study concludes to ensure allocation concealment. Access to the randomization codes will be restricted until final data analysis to maintain blinding integrity.

### Blinding

To ensure blinding in this study protocol, double - blind tests will be employed. Specifically, sham paroxetine and sham CHSGS capsules will be prepared. The Pharmacy Department of the Hospital of Chongqing Traditional Medicine Hospital will handle and label the medications in a special way. This is to guarantee that both the patients and the practitioners involved in the study remain completely unaware of the identity of the treatment being administered. Moreover, all practitioners are prohibited from communicating with the participants about the information related to this trial.

### Intervention

We prepared two colors of capsules, red capsules three times a day and yellow capsules once a day. Within the different groups, the contents of the different capsules were different.

### CHSGS group

Patients will be provided three-daily treatment with 5 g CHSGS added to the 5 red capsules and one-daily treatment with 5 g mixed starch powder added to the yellow capsule each time until 4 weeks.

The CHSGS preparation contained the gathering of the following components: 10 g Chaihu 12 g Shaoyao 12 g Zhiqiao 6 g Zhigancao 10 g Chenpi 10 g Chuanxiong and 15 g Xiangfu (Fan et al., 2023). They are made into a gel bags 100 pills per bottle made by the Pharmacy Department of Chongqing Traditional Chinese Medicine Hospital to meet the quality requirements of the Pharmacopoeia of the People’s Republic of China (2015 edition). The individual components of CHSGS, underwent decoction in boiling water for 30 min. After that, they were concentrated and then vacuum - dried to form a paste. Subsequently, these pastes were combined to create a new paste with a concentration of 8 g of crude extracts per gram. Next, starch powder was added to a container. The mixture was stirred thoroughly and then processed into capsules.

### Paroxetine group

Patients will be provided three-daily treatment with 5 g mixed starch powder added to the 5 red capsules and one-daily treatment with 30 mg paroxetine added to the yellow capsule each time until 4 weeks.

Dapoxetine and paroxetine are both 5-HT reuptake inhibitors for the treatment of premature ejaculation, however, dapoxetine is not recommended for daily administration, so that it is therefore difficult to observe its effects on the central nervous system. Also a trail showed that an on-demand dose of 30 mg dapoxetine is no more effective than the currently prescribed paroxetine treatment (Simsek et al., 2014). So we choose paroxetine as the positive control group as well as the treatment group. Smashed paroxetine will be mixed with starch powder and stir well into a container in order to be made into capsule.

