Therefore, in this protocol, we plan to perform a double-blind randomized controlled trial, aiming to:1. Compared with the placebo and paroxetine, CHSGS will be as the same effective to the treatment for APE.2. Compared with paroxetine alone, CHSGS and combination of drugs will be more effective due to its specific effects.3. Investigate the influence of paroxetine or/and CHSGS capsule treatment on the brain activities of patients with APE compared with that of placebo treatment by fMRI and analyze the possible correlations between the changes of cerebral activity and the improvement of clinical variables in each group so as to explore how the paroxetine and CHSGS capsule manages depression by modulating brain function to treat APE.

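### Paroxetine is named the positive control, yet no stated aim tests it against placebo on IELT, and aim 1 as worded would be met by a trial in which no arm separates from placebo

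*Protocol article*

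**What the plan says.** All references are to the protocol article.

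- **Role of paroxetine** (Paroxetine group): "So we choose paroxetine as the positive control group as well as the treatment group".
- **Aim 1** (end of the Introduction): "Compared with the placebo and paroxetine, CHSGS will be as the same effective to the treatment for APE".
- **Aim 2** (same place): "Compared with paroxetine alone, CHSGS and combination of drugs will be more effective due to its specific effects". Placebo does not appear.
- **Aim 3** (same place) studies paroxetine, CHSGS or both "on the brain activities of patients with APE compared with that of placebo treatment by fMRI". Clinical variables enter only through their correlation with brain changes within each group.
- **Primary clinical outcome** (Primary outcome): change from baseline in "the intravaginal ejaculatory latency time (IELT) measured using a stopwatch", alongside brain MRI.
- **Analysis** (Clinical variables analysis): a list of tests that includes "an independent samples t - test, and a two - sided test", and the rule "A P - value <0.05 will be considered statistically significant". The section names no between-arm contrast, gives no criterion for sameness and attaches no condition to the aim 1 claim.
- **Allocation** (Randomized): "Eligible participants will be randomly allocated to one of four groups in a 1:1:1:1 ratio". One of the four groups is placebo, and Table 1 schedules IELT at enrolment and week 4.

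**The concern.** A positive control with a concurrent placebo arm lets a trial show that it could detect a working treatment. This trial has both arms, but its clinical aims never put them side by side on IELT. A finding that CHSGS resembles paroxetine is therefore not tied to paroxetine having worked in these patients.

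The wording of aim 1 adds to this. Taken literally, it expects CHSGS to be the same as placebo and the same as paroxetine. If all three arms end up alike, the aim is met, although that is also what a trial that failed to detect anything looks like. At stake is a statement that a herbal formula matches an established drug, made from data in which neither was shown to do anything.

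**Working it through.** **The plan's own figure.** Study design gives 21 per group and four groups: 4 × 21 = 84, as stated. The 21 allows for losses from an imaging minimum of 15 per group, which implies a loss of 1 − 15/21 = 28.6%. No IELT effect, SD or power is given, so there is no IELT calculation to reproduce.

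**Where each pair of arms meets**

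| Contrast | On IELT or clinical effect | On fMRI |
|---|---|---|
| CHSGS vs placebo | aim 1, worded as the same | aim 3 |
| CHSGS vs paroxetine | aims 1 and 2 | – |
| Combination vs paroxetine | aim 2 | – |
| Paroxetine vs placebo | **none** | aim 3 |

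**Power of the missing contrast.** Inputs: n = 21 per arm (Study design), two-sided 0.05 (Clinical variables analysis), and an effect of d SD (assumed). A two-sample t test has 2 × 21 − 2 = 40 degrees of freedom, critical value 2.021 and non-centrality d × √(21/2) = 3.24d.

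- d = 0.5: non-centrality 1.62, power 35%
- d = 0.8: non-centrality 2.59, power 72%
- d = 1.0: non-centrality 3.24, power 89%
- d = 1.5: non-centrality 4.86, power 99.7%

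The smallest effect with 80% power is 0.89 SD. The 95% confidence interval for CHSGS minus paroxetine has half-width 2.021 × √(2/21) = 0.62 SD.

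**How often an uninformative sameness arises.** This is a simulation of three normal arms with SD 1, 21 per arm, and CHSGS and placebo both with mean 0. Two assumptions are not in the article: the paroxetine effect, and reading P ≥ 0.05 as sameness.

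| True paroxetine effect (SD) | CHSGS vs paroxetine not significant | …and paroxetine has not beaten placebo |
|---|---|---|
| 0 | 95% | 91% |
| 0.3 | 84% | 75% |
| 0.5 | 65% | 49% |
| 0.8 | 28% | 14% |
| 1.0 | 11% | 4% |
| 1.5 | about 0% | about 0% |

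At the imaging minimum of 15 per arm, the last column becomes 80%, 61% and 28% at 0.3, 0.5 and 0.8 SD, and 12% at 1.0 SD.

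**What different conditions leave behind.** The table uses the same setup (inert CHSGS, 21 per arm). It shows trials in which CHSGS still looks the same as paroxetine.

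| Condition for the claim | 0.3 SD | 0.5 SD | 0.8 SD |
|---|---|---|---|
| None | 84% | 65% | 28% |
| Paroxetine beats placebo | 9% | 16% | 14% |
| CHSGS beats placebo | 2.4% | 2.3% | 1.8% |

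Requiring both conditions cannot exceed the last row.

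**With a formal margin instead.** If both drugs are truly inert, an equivalence test with 21 per arm passes in about 4% of trials at a margin of 0.5 SD, and in 63% to 88% at margins of 0.8 to 1.0 SD. All these margins are illustrative; the article states none.

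**The case against.** The strongest reply is that contrasts, their order and any gatekeeping belong in a statistical analysis plan, which is not shown, and that a journal article condenses. The design has what is needed: a randomised placebo arm, IELT in every patient, and suitable tests in the list. This stands in part. The article does not exclude the comparison, and an unseen plan may contain it. It does not remove the point, because the article does state its aims, and the stated set is what goes wrong. An analysis plan that followed aim 1 literally would accept a trial with no effect anywhere.

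A second reply is that aim 1 names placebo as a comparator and probably means superiority over it. If so, the failure nearly vanishes. CHSGS above placebo, CHSGS not different from paroxetine and paroxetine not above placebo occur together in only 1.0%, 0.5% and 0.1% of trials at 0.3, 0.5 and 0.8 SD. This is a fair reading of the intent, but the article does not say it. It also shows that a CHSGS-versus-placebo condition does most of the protective work.

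A reader might go further and infer three things that the documents do not support:

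- *That this outcome is likely.* No IELT effect or SD is given, the Discussion presents paroxetine as effective, and the risk is about 4% at 1.0 SD and near zero at 1.5 SD.
- *That the plan would certainly report it as support for CHSGS.* No rule for declaring sameness is stated.
- *That the problem is wholly separate from the missing margin.* Most of the percentages come from treating non-significance as sameness. With a margin of 0.5 SD, inert arms would pass in only about 4% of trials; the exposure persists at wide margins.

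**Conclusion.** The point holds as a defect in the stated aims. Paroxetine is given the role of positive control, no clinical aim uses it as one, and aim 1 as worded is met when no arm separates from placebo on IELT. The data for the missing contrast will be collected, so the defect lies in the wording and not in the design.

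The size depends on the true paroxetine effect. With inert CHSGS, 21 per arm and non-significance read as sameness, it runs from about 75% of trials at 0.3 SD to about 0% at 1.5 SD. The document does not allow a choice within that range.

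It might also be inferred that a positive paroxetine-versus-placebo test alone would settle the matter. It would not: 9% to 16% of trials would still show a false sameness. Calling the CHSGS–paroxetine comparison uninformative whenever that test fails would also go too far. If both drugs truly work equally at 0.5 or 0.8 SD, CHSGS beats placebo and does not differ from paroxetine, while paroxetine misses significance against placebo, in about 13% and 12% of trials.

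**What to change.** Reword aim 1, and add to Clinical variables analysis, so that three IELT contrasts are named:

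1. Paroxetine versus placebo, superiority, two-sided 0.05.
2. CHSGS versus placebo, superiority, two-sided 0.05.
3. CHSGS versus paroxetine, reported as a difference with its confidence interval.

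Allow the statement that CHSGS is as effective as paroxetine only if CHSGS beats placebo and paroxetine is also shown to beat placebo. If CHSGS beats placebo and paroxetine does not, report the CHSGS–placebo result and give the CHSGS–paroxetine difference with its interval, without an equivalence claim.

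**Cost.** This changes wording only. It uses arms already randomised and IELT already scheduled, with no added patients, visits or measurements. The price is that the statement is lost more often. If both drugs truly work equally, paroxetine fails to beat placebo in about 100 − 35 = 65% of trials at 0.5 SD and 100 − 72 = 28% at 0.8 SD. Because CHSGS must also beat placebo, the total loss is larger.

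**What it does not do.** The condition does not replace an equivalence or non-inferiority margin. As an illustration, a non-inferiority test at one-sided 0.025 with 80% power needs 63 per arm for a margin of 0.5 SD and 25 per arm for 0.8 SD, against the 21 planned.
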